## Assignment of interventions: allocation

### Sequence generation {16a}

Individual randomisation takes place using SAS PROC PLAN via a permuted-block randomisation method stratified by site only. Block sizes vary at 4 and 6. The randomisation code has 11-digit numbers: the first 3 digits for protocol (the same across all participants at all sites ‘106’), the next 3 for site, the next 4 for participants within each site, and the final digit is a check-digit to reduce the risk of misidentification between participants.

### Concealment mechanism {16b}

Randomisation lists are created for each site by an independent statistician, and each list is housed on the electronic data capture system (EDC) for that particular site and is inaccessible to trial staff except to randomise the next eligible participant. Randomised allocation for each trial participant is provided to trial staff by extracting the next available randomisation allocation, obtained from the randomisation list for that site housed on the database. Upon confirmation of eligibility criteria and completion and entry of the informed consent details, the EDC system selects the next available randomisation slot and presents the details of the selection to the study doctor/nurse on screen.

### Implementation {16c}

Internally, the EDC selects against an electronic randomisation list prepared in advance by the statistician. The EDC guarantees to make the selection in the natural order of the list, filtering by study site only. Once a selection is made, the randomisation record is tagged with the participant study allocated identifier, date and time of randomisation and other EDC system audit values (username, machine name, etc.). A tagged record cannot be selected more than once. A study doctor makes the final assessment of eligibility for enrolment and participation once all inclusion and no exclusion criteria have been met. Either a study doctor or nurse may then capture this information in the EDC screening form. If the responses to this form indicate eligibility, the informed consent can be recorded and, once completed, the participant is enrolled, and the randomisation arm is assigned automatically and displayed on-screen.

## Assignment of interventions: blinding

### Who will be blinded {17a}

Participants randomised to the control arm (the recommended standard of care in South Africa and Tanzania) receive a simple once-daily dose of fluconazole, while those randomised to the intervention arm will receive flucytosine in addition (4 doses per day). Any potential for bias in this open-label pragmatic trial will be minimised with the use of an objective primary endpoint of all-cause mortality at 6 months. Adding 6-hourly placebos to the control arm would greatly complicate the regimen used in the control arm. This may bias the trial results in favour of the intervention regimen which could be more to do with the complexity of the control arm than the potency/efficacy of the regimens. There is no perfect way of measuring adherence to these antifungal drugs, and so if the control arm is made inferior because of the complexity of the trial design, this would not be known.

The trial statistician is blinded regarding the treatment code when developing the statistical analysis plan and writing the statistical analysis programmes, which are validated and completed using dummy randomisation codes.

### Procedure for unblinding if needed {17b}

The trial is open-label. However, investigators are blinded to aggregate data and unblinding of these aggregate data is only permissible with consent of the Trial Steering Committee.

## Data collection and management

### Plans for assessment and collection of outcomes {18a}

Electronic case report form (eCRF) data collected and validated using the EDC is stored in an electronic database that is protected using a scheme of authentication and encryption. Paper documents, such as clinical notes and administrative documentation, are kept in a secure location (for example locked filing cabinets in a room with restricted access).

The EDC is set up such that a standard visit schedule is pre-populated with all relevant eCRFs per visit (including all required procedures and assessments per protocol), with a visit calendar. When a visit is commenced, all CRFs are immediately available. Additional CRFs are available if needed, and additional unscheduled visits can be created where applicable. Each visit, and each CRF within a visit, can only be completed once per participant.

### Plans to promote participant retention and complete follow-up {18b}

On days 1 and 15, participants are seen in person and compensated for their time, inconvenience and out-of-pocket expenses (mainly transport to site). Beyond day 15, study follow-up is telephonic unless in-person visits are required for clinical indications. The PIS/ICF also informs participants that, should they be unreachable, we may access their medical records to assess vital status and identify any incident cases of cryptococcal meningitis during the 6 months of follow-up. In addition, we may access population (vital status) registers to identify any missed deaths. Compensation for the time taken to complete these telephonic follow-up calls is provided in the form of electronic voucher codes sent to the participant by short message system (SMS).

All compensation for study visits is in line with local compensation models outlined by the regulatory authorities and/or ethics committees.

If no vital status assessment can be made by study close, then the participant is considered lost to follow-up (LTFU).

### Data management {19}

A detailed Data Management Plan has been developed for this trial.

No data are stored on the devices used to access the EDC. Electronic archives are maintained, secured and backed up according to University College London’s (UCL) Archiving Standard Operating Procedure.

The EDC can only be accessed by an authenticated user with user-level permissions. Study staff are provided with mobile internet routers so that live entry is always possible.

The case report forms (CRFs) in the EDC have in-built validations which check within and across forms to minimise errors, and incomplete forms or forms with errors cannot be saved until completed correctly.

Data are downloaded every fortnight and queries run in Stata to identify any missing data, outliers or conflicts, and listings shared with the sites to check and resolve if needed.

### Confidentiality {27}

All participants are assigned a screening identification number (SID) before enrolment and a trial participant identification number (PID), if randomised. All records in the EDC are stored under these SIDs and PIDs. Personal identifiable information values are encrypted and can only be viewed via the EDC and only for validated users. The database is effectively anonymised at rest and in motion. Paper records are anonymised and personal details replaced with the study PID. Only the participant information sheet/informed consent form (PIS/ICF) has both the participant’s name and their study PID. These are kept in a separate file, in a lockable cabinet in an access-controlled study office at each site.

Specimens collected for study storage are collected using the study PID only.

### Plans for collection, laboratory evaluation and storage of biological specimens for genetic or molecular analysis in this trial/future use {33}

Several sub-studies are planned or underway, which make use of stored samples collected during the trial. These include qPCR (cryptococcal nucleic acids) of blood and cerebrospinal fluid, HIV-1 viral load and viral resistance, antiretroviral drug levels, immunogenetics, blood and cerebrospinal fluid factors related to host inflammatory response and organism that might explain the lack of symptoms or signs in subclinical cryptococcal meningitis, and antifungal resistance studies in individuals with antigenaemia who develop symptomatic cryptococcal meningitis while on pre-emptive treatment. Explicit consent is obtained from participants for storage of these samples.

## Statistical methods

### Statistical methods for primary and secondary outcomes {20a}

A detailed, statistical analysis plan (SAP) has been developed. Briefly, the primary analysis will compare the two treatment groups in terms of the proportion of participants who have died from any cause within 6 months from randomisation. A log binomial model (generalised linear model [GLM]) will be used to analyse the primary endpoint, including treatment arm as the sole predictor, to derive the unadjusted relative risk (RR) of 6-month all-cause mortality between intervention and control and the associated 95% confidence intervals (CI).

Covariate adjusted analysis will be performed within the GLM framework including pre-specified covariates: Country, CD4, lumbar puncture at baseline, age, sex, baseline ART status and CrAg titre/semi-quantitative CrAg score group. Subgroup analysis will also be performed for these pre-specified covariates. For the primary outcome, binomial distribution and log link functions will be used, and imputation for baseline missing covariates will be made for the covariate-adjusted analysis. Sensitivity analyses of the primary endpoint making different assumptions for the losses to follow-up and additional per protocol population will be conducted.

Secondary endpoints will also be analysed using GLMs with the treatment arm as the sole predictor. The point estimate of the treatment effect with 95% CI will be derived via specification of a GLM for each secondary outcome, depending on its distribution. For a binary endpoint, the GLM with binomial distribution and log link function will be estimated, and the treatment effects measured as RR. For a continuous outcome, a Gaussian distribution will be assumed, and the identity link function will be used. Correspondingly, the mean difference and its 95% CI between two arms will be calculated. For a count outcome, Poisson distribution and log link function will be used, from which the incidence rate ratio (IRR) and its 95% CI will be computed.

Treatment effects will be analysed and modelled across the range of baseline antigen titres and semi-quantitative titre results as detailed in the Statistical Analysis Plan, and as has been done across the spectrum of meningitis severity in the ACTA and AMBITION-cm trials [32].

Analyses of survival data will be conducted using unadjusted and adjusted Cox regression analysis to calculate the hazard ratio (HR) and 95% CI between the treatment groups. Kaplan-Meier survival curves will also be plotted by treatment group, from which survival rates at 10 weeks and 6 months will be derived. A log-rank test will be performed to compare the survival curves between the treatment groups.

Primary analyses of efficacy outcomes will be based on the intention-to-treat population, and secondary analyses will be based on the per-protocol population. The safety analysis will be on the safety population. The frequency and proportions of participants developing clinical and laboratory-defined side effects (DAIDS grade 3 or 4 adverse events) will be summarised by treatment arm.

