Among individuals identified with cryptococcal antigenaemia through screening, the risk of having subclinical meningitis and of death is both strongly associated with the antigen titre [28, 29]. Therefore, it may be that the benefit of enhanced antifungal therapy will be more marked in those with higher blood CrAg titres. In addition, a lateral flow semi-quantitative cryptococcal antigen test is now available that could enable implementation of a stratified approach to antifungal therapy based on antigen level.

Therefore, the balance of risks and benefits of more intensive antifungal therapy in the blood CrAg-positive population is not known, and robust data on the impacts of combined treatment, across the range of blood antigen titres, are urgently required.

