### Sample size {14}

Based on evidence from recent studies, we assume that the combined regimen of fluconazole plus flucytosine (intervention arm) could lead to a 40% relative reduction in mortality compared with fluconazole alone. From the ACTA trial [2, 31], the oral combination treatment had a mortality rate of 35% at 10 weeks, compared with 55%–70% mortality of fluconazole alone observed in clinical settings (i.e. a reduction of at least 36% mortality). We assume that 30% of blood CrAg-positive individuals identified during screening and treated with fluconazole alone die. This assumption is inferred from published data, including the REMSTART trial [15] in which 32% of blood CrAg-positive individuals treated with fluconazole (CD4 < 200 cells/µl) died over 6 months of follow-up. In South Africa, mortality was 25% in 2 cohort studies [16, 17].

Using a two-sided *α* = 0.05, a sample size of 540 (270 per arm) will provide 91% power to detect a 40% relative reduction in mortality with fluconazole alone versus flucytosine plus fluconazole (i.e. an observed mortality of 30% vs. 18%, respectively). The trial will also have 81% power to detect a 35% relative reduction if the effect size is smaller, and 83% power if mortality in the fluconazole arm is lower at 25%. Loss to follow-up was 2.5% in the REMSTART trial [15] over 12 months and <1% in the ACTA trial [2] over 10 weeks. A target of 600 participants will be enrolled, to conservatively account for up to 10% loss to follow-up in a pragmatic trial embedded in routine programmes.

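### The primary 6-month RR uses treatment arm alone, so it forgoes modest precision available from site, the randomisation stratum, and from baseline CrAg titre

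*Protocol article*

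**What the plan says.** - **Primary model** (Statistical methods {20a}): a log-binomial GLM "including treatment arm as the sole predictor, to derive the unadjusted relative risk (RR) of 6-month all-cause mortality".
- **Supporting model** (same section): a covariate-adjusted GLM with "pre-specified covariates: Country, CD4, lumbar puncture at baseline, age, sex, baseline ART status and CrAg titre/semi-quantitative CrAg score group", with imputation of missing baseline covariates. Subgroup analyses on these covariates and modelling of effect across titres are also planned.
- **Randomisation** (Sequence generation {16a}): "permuted-block randomisation method stratified by site only". Study setting {9} gives 11 sites in two countries.
- **Prognosis** (Background and rationale {6a}, on combination treatment): among people with screened antigenaemia, "the risk of having subclinical meningitis and of death is both strongly associated with the antigen titre".
- **Power** (Sample size {14}): "a sample size of 540 (270 per arm) will provide 91% power" for "an observed mortality of 30% vs. 18%, respectively", and "81% power to detect a 35% relative reduction if the effect size is smaller, and 83% power if mortality in the fluconazole arm is lower" (the lower control rate being 25%). This is a two-proportion comparison without covariates, so it matches the arm-only primary model.

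**The concern.** Two separate pieces of information are left out of the confirmatory estimate.

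**Site.** Stratified randomisation balances the arms within site. An arm-only model does not credit that balance in its standard error. If mortality differs between sites, the crude test is somewhat conservative. Country, used in the adjusted model, is a coarser version of the stratum.

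**Titre.** Allocation is not stratified by titre, so the arms can differ on it by chance. The protocol itself names titre as strongly associated with death, plans to model it and plans to impute missing covariates, but the headline RR makes no use of it. If the crude and adjusted results disagree, the crude one is confirmatory by rule.

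What is at stake is the width of the main confidence interval and the robustness of the main estimate. The validity of the test is not in question.

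**Working it through.** **1. Reproduce the stated powers.** Inputs from Sample size {14}: 270 per arm, two-sided alpha 0.05. Power = Φ[(d − 1.96·SE0)/SE1], with SE0 = √(2p̄(1−p̄)/270) and SE1 = √((p1(1−p1)+p2(1−p2))/270).

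- 30% vs 18%: SE0 = 0.03676, SE1 = 0.03639; (0.12 − 0.07204)/0.03639 = 1.318, power 90.6% (stated 91%).
- 30% vs 19.5%: (0.105 − 0.07280)/0.03687 = 0.873, power 80.9% (stated 81%).
- 25% vs 15%: (0.10 − 0.06748)/0.03416 = 0.952, power 83.0% (stated 83%).

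540/0.9 = 600 reproduces the enrolment target. A Wald test on the log RR gives 89.2%, 79.5% and 81.4%, so the choice of test alone moves power by about 1.5 points.

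**2. Rough upper guide.** Suppose covariates explain a share R² of outcome variance (assumed; the documents give none). Multiplying both SEs by √(1−R²):

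| R² | 30 vs 18 | 30 vs 19.5 | 25 vs 15 | 540/(1−R²) |
|---|---|---|---|---|
| 0 | 90.6% | 80.9% | 83.0% | 540 |
| 0.05 | 92.0% | 82.8% | 84.8% | 568 |
| 0.10 | 93.3% | 84.8% | 86.7% | 600 |

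This is optimistic. It ignores the cost of fitting the covariate terms, and the crude estimate already benefits from site balance.

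**3. Simulation of the design.** 540 participants, 11 sites, permuted blocks of 4 and 6, 1,500 replicates per row. The crude log RR is compared with a standardised log RR from a logistic model with arm, site, titre and CD4. Strengths are assumed, as OR per SD for titre and CD4 and logit SD for site. The Monte Carlo SE of each power is about 0.7 points.

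| Titre / CD4 / site SD | Mortality | Power crude → adjusted | Variance ratio adjusted/crude |
|---|---|---|---|
| 1.0 / 1.0 / 0 | 30 vs 18 | 91.5 → 90.8% | 1.009 |
| 1.3 / 1.2 / 0.2 | 30 vs 18 | 90.9 → 92.3% | 0.977 |
| 1.6 / 1.3 / 0.3 | 30 vs 18 | 90.5 → 91.9% | 0.962 |
| 2.0 / 1.4 / 0.3 | 30 vs 18 | 90.2 → 92.8% | 0.935 |
| 1.6 / 1.3 / 0.3 | 25 vs 15 | 83.1 → 85.0% | 0.971 |
| 1.6 / 1.3 / 0.3 | 30 vs 19.5 | 81.5 → 83.8% | 0.969 |

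The gain is 1.4 to 2.6 points where covariates are prognostic. Where they are not, the difference is within Monte Carlo error. Type I error was 4.4% to 5.1% crude and 4.7% to 4.9% adjusted.

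A further simulation over titre OR 1.3 to 2.0, with a small-sample-corrected SE, gave crude-to-adjusted variance ratios of about 1.02 to 1.10. That is a reduction of 1 − 1/1.02 = 2% to 1 − 1/1.10 = 9%, equivalent to 540 × 0.02 = 11 to 540 × 0.10 = 54 extra participants. At the top of the range the power gain is less certain: one run of 1,200 replicates at 30% vs 19.5% with titre OR 2.0 gave 80.8% → 85.3%.

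**4. Chance titre imbalance.** The SD of the between-arm difference in mean standardised titre is √(2/270) = 0.086, so the 95% limit is 1.96 × 0.086 = 0.169 SD. The shift in log RR is roughly 0.169 × ln(OR) × (1 − 0.24), taking mean mortality as 24%. This is 0.034 at OR 1.3 and at most about 0.089 at OR 2.0, or about 3% and 9% on the RR.

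**The case against.** The strongest reply is that nothing here is wrong. The sample size assumes an unadjusted comparison, the primary model delivers one, and the test holds its size. An adjusted RR with titre is already pre-specified, so a titre imbalance would be seen and corrected there. On this view the dispute is only which of two planned estimates leads. All of that stands, and it limits the point to efficiency and robustness. It does not explain why the stratification factor is in neither described model, or why the factor that the protocol calls strongly associated with death stays out of the confirmatory estimate.

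Four stronger readings are tempting but unsupported:

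- *That power is lost from the stated 81%.* That 81% is already the crude test's power; adjustment would add to it.
- *That site is in no analysis at all.* The section is a summary and refers to a detailed SAP that is not shown. Only the models described can be judged.
- *That CD4 is strongly prognostic here.* The protocol says this of titre only, and entry is restricted to CD4 below 100.
- *That the gain is like a 6% to 17% larger sample.* Such figures arise from comparing mean estimated SEs when the adjusted SE is not corrected for the fitted terms. In a check with covariates of no prognostic value, that SE ratio was 1.022 while the empirical variance ratio was 0.995. Where the SE ratios were 1.06, 1.11 and 1.15, the empirical ratios were 1.02, 1.05 and 1.12.

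Timing is also a fair objection. Trial status expected recruitment to finish in October 2025, the article is dated March 2026, and the trial statisticians produce the DMC reports in an open-label trial. A late change of primary estimator must be shown to be independent of the results. That governs how the change is made; it does not remove the reason for it.

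**Conclusion.** The point holds as a modest efficiency and robustness improvement. The arm-only analysis is valid and adequately powered on the plan's own inputs. Under the assumed strengths (titre OR 1.3 to 2.0 per SD, site SD 0.2 to 0.3 on the logit scale), adjusting for site and titre would lower the variance of the log RR by about 2% to 9% and add about 1 to 3 points of power. The gain would be larger only if titre is very strongly prognostic. These strengths are assumptions, since the documents quantify none of them. The simulated models also included CD4, but the conclusion does not depend on it. The benefit is most useful in the 81% and 83% scenarios. The second is realistic, because Sample size {14} cites 25% mortality in two South African cohorts.

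**What to change.** Before database lock, and without sight of results by arm:

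- Make the primary estimate a marginal (standardised) 6-month RR from a logistic model with arm, site (small sites pooled within country) and baseline CrAg titre or semi-quantitative score group, choosing one form of the titre variable in advance. CD4 may be added, as it is already a pre-specified covariate.
- Use a robust or delta-method CI with a small-sample correction.
- Keep the crude log-binomial RR as a sensitivity analysis.

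Standardisation keeps the relative-risk measure named in Outcomes {12}. It also avoids the convergence problems that a log-binomial model with many terms can meet.

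The cost is protocol and SAP wording, plus two obligations. First, missing baseline titres must be imputed for the primary analysis, by extending the imputation already planned for the adjusted one. Some may be missing, because the event schedule lists a routine CrAg test but no separate titre assay, and sample storage can be declined (an inference from the documents). Second, the record should state who made the change, when, and that they had not seen results by arm.

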### Interim analyses {21b}

No interim analysis is planned. The Data Monitoring Committee reviews safety and outcome data every 6 months and can recommend premature closure or reporting of the trial, or that recruitment to any research arm be discontinued.

### Methods for additional analyses (e.g. subgroup analyses) {20b}

A separate economic analysis plan has been developed. Briefly, an economic analysis will be conducted based on the ITT population. The objective is firstly to determine the relative cost-effectiveness (or efficiency) of the combined therapy versus monotherapy, including screening and early treatment. Standard procedures will be carried out during data collection through the CRF, interviews with staff, during data analysis and probabilistic modelling, using the CHEERS economic guidelines and based on GCP. Secondly, the economic analysis will assess the individual costs of accessing and receiving care, collected through CRFs. The analysis will be performed to demonstrate the societal perspective including both health system costs and household levels on out-of-pocket expenditures. Cost-outcome measures will include annualised health care cost, cost per disability-adjusted life years (DALYs) averted and life years lost, cost offsets and household financial burden per individuals.

